## 2 STUDY OVERVIEW

[figure not shown]

PHPT = primary hyperparathyroidism; MIP = minimally invasive parathyroidectomy; BCE = bilateral cervical exploration

### 112 3 STUDY FLOW CHART

|                                                                                                                       | Before inclusion         | Before Surgery           | Surgery                     | At 1 and 6 months post-surgery |
|-----------------------------------------------------------------------------------------------------------------------|--------------------------|--------------------------|-----------------------------|--------------------------------|
| Informed Consent                                                                                                      |  |                          |                             |                                |
| History of the disease                                                                                                |  |                          |                             |                                |
| Physical examination (weight, height)                                                                                 |  |                          |                             |                                |
| Pregnancy test (urine or blood)
(within the previous 8 days)                                                       |  |                          |                             |                                |
| Cervical ultrasound                                                                                                   |  |                          |                             |                                |
| Blood tests*                                                                                                          |  |                          |                             |        |
| F18-choline PET-CT and/or MIBI SPECT-CT
(within 12 weeks prior to surgery; at least 48 hours between the 2 exams)  |                          |  |                             |                                |
| For patients undergoing a PET-choline examination, a telephone call the day after the examination to assess tolerance |                          |  |                             |                                |
| Adverse events                                                                                                        |                          |  |     |        |
| Patient satisfaction (EVAN-G questionnaire)                                                                           |                          |                          |  ** |                                |

113  
114 \* Biochemistry: Calcium, phosphoremia, albumin, creatinine, PTH, 25 OH vitamin D

115 \*\*completed within 4 to 48 hours after surgery, before discharge from hospitalization

## 4 SCIENTIFIC RATIONALE OF THE STUDY

### 4.1 BACKGROUND

Primary hyperparathyroidism is a common endocrine disease, related to autonomic overproduction of parathyroid hormone (PTH), usually by a parathyroid adenoma (PTA). The diagnosis is confirmed by a laboratory test. Excision of PTA remains the only curative treatment: despite a diagnosis often at an asymptomatic stage, normalization of hypercalcemia by excision of PTA improves bone mineral density and quality of life of patients. Bilateral cervical exploration of the parathyroids is now supplanted by minimally invasive surgery requiring precise localization of the PTA preoperatively. This minimally invasive technique, usually performed on an outpatient basis under local anesthesia, is associated with a better cure rate and fewer complications than bilateral cervical exploration, and at a lower cost (Udelsman-2011).

The current diagnosis to localize PTA is based on Tc99m-sestaMIBI (MIBI) scintigraphy with tomographic acquisition and CT scanning, negative in 33% of cases, leading to the proposal of bilateral cervical exploration (Ciappuccini-2012).

The recent literature and the results of our prospective APACH1 study (NCT02432599) strongly suggest the best diagnostic value of positron emission tomography coupled with F18-choline (FCH) CT scanning. Out of 25 patients with primary hyperparathyroidism and a negative MIBI scan, second-line FCH PET/CT was positive in 19 patients guiding parathyroidectomy and successfully reduced operative time in the majority of patients (Quak-2017).

Although FCH PET/CT is not yet used as a first-line treatment for primary hyperparathyroidism (cost of examination, availability of PET cameras, lack of marketing authorization for FCH in this indication), its contribution to guiding the surgical procedure seems promising. It therefore seems interesting to question the place of FCH PET-CT as a first-line imaging technique to localize PTA in biologically confirmed primary hyperparathyroidism, while taking into account the costs.

The delay to perform PET-CT images after FCH injection varies depending on the team (from 0 to 2 hours, some favouring 30 min images, others 60 min and others two acquisitions at 5 and 60 min) (Treglia-2018). Few studies have compared two acquisition times, one early (5-15 min) and the other later (60 min). A retrospective study conducted on 43 patients shows better contrast from 60 min post-injection (Rep-2015). Another study describes an increase in SUVmax at late time on a preliminary study, but data are limited (Thanseer-2017). However, other authors have found good performance in <15 min imaging (Michaud-2014; Prabhu 2018). The advantage of early imaging after injection would be to avoid a waiting time of one hour in an injection box for the patient and to allow better management of the organization of the PET program of a nuclear medicine department. It therefore seems interesting to prospectively evaluate two PET-CT imaging times at the FCH and to compare them in terms of detection sensitivity and semi-quantitative analysis.

### 4.2 ORIGINALITY AND INNOVATION

In accordance with the recommendations on the methodology of evaluating diagnostic techniques (Rodger, Trials, 2012), we propose the first prospective randomized study comparing 2 diagnostic strategies (MIBI SPECT/CT or FCH PET/CT) first-line for the preoperative localization of PTA.

We seek to evaluate the best first-line diagnostic strategy to localize PTAs and guide surgery, at the lowest cost to society, by comparing the 2 strategies in terms of efficacy and cost of each strategy.

We hypothesize that FCH PET/CT will reduce the proportion of unnecessary invasive surgery decisions and that the higher cost of PET scan compared to MIBI will be offset by a lower cost in terms of the type of surgery performed correctly and complications.

### 4.3 EXPECTED BENEFIT TO THE PATIENT

Insofar as the only treatment with curative aim remains surgical excision of the PTA, the challenge of being able to locate the PTA prior to the surgical procedure is major to guide the surgery. While minimally invasive surgery, associated with more cures and fewer complications, as well as lower cost, is preferred, it is only possible if the PTA is previously localized. However, to date, MIBI scintigraphy combined with SPECT/CT is not contributory for a third of patients, for whom bilateral cervical exploration is therefore proposed.

We hypothesize that first-line FCH PET/CT will reduce the proportion of unnecessary invasive surgery decisions and that the higher cost of PET scanning compared to MIBI will be offset by a lower cost in terms of the type of surgery performed appropriately and complications. If we test this hypothesis by prospectively randomizing two diagnostic strategies, as recommended to evaluate diagnostic techniques (Rodger, Trials, 2012), the use of FCH PET/CT as a first-line treatment to localize PTA could be considered to improve the therapeutic management of patients, at a lesser cost to the community.

## 5 STUDY OBJECTIVES

### 5.1 PRIMARY OBJECTIVE

The primary objective is to compare, between each diagnostic strategy, the proportion of patients for whom the first-line imaging technique (MIBI SPECT/CT or FCH PET/CT) guided the surgical procedure appropriately (true positive minimally invasive surgery decision and patient cure).

### 5.2 SECONDARY OBJECTIVES

The secondary objectives are to:

- Conduct a medico-economic evaluation comparing the costs and effectiveness of the two diagnostic strategies
- Estimate the diagnostic performance of each strategy
- Assess the number of failures at 6 months of parathyroid surgery (regardless of the type of surgery performed) for each strategy
- Assess post-surgical complications
- Assess intra- and inter-observer variability for the interpretation of FCH PET/CT and MIBI SPECT/CT
- Explore the relationship between the positivity of imaging tests, including FCH PET/CT, and serum PTH concentration at baseline
- Evaluate the detection performance of FCH PET-CT on an early imaging time point at 10 min post-injection compared to that of acquisition at 60 min.
- Assess patient satisfaction in the perioperative period

## 6 ENDPOINTS

### 6.1 PRIMARY ENDPOINT

The primary endpoint of the study is the proportion of patients for whom the **first-line** imaging technique (MIBI SPECT/CT or FCH PET/CT) was able to guide the surgical procedure appropriately defined by:

- A decision to perform a truly positive (wise) minimally invasive surgery
- AND**
- Achieving a cure for the patient, defined as normalization of serum calcium at one month post-surgery

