|                           | Secondary objectives 
 
- To conduct a medico-economic evaluation comparing the costs and effectiveness of the two diagnostic strategies
 
- To estimate the diagnostic performance of each strategy
 
- To assess the number of failures at 6 months of parathyroid surgery (regardless of the type of surgery performed) for each strategy
 
- To assess post-surgical complications
 
- To assess intra- and inter-observer variability for the interpretation of FCH PET/CT and MIBI SPECT/CT
 
- To explore the relationship between the positivity of imaging tests, including FCH PET/CT and serum PTH concentration at baseline
 
- To evaluate the detection performance of FCH PET/CT at an early imaging time point at 10 min post-injection compared to that of 60 min post-injection.
 
- To assess patient satisfaction in the perioperative period
 
 |
| Judgement criteria | Main criterion
Proportion of patients for whom first-line imaging technique (MIBI SPECT/CT or FCH PET/CT) guided the surgical procedure appropriately as defined by: 
 
- A decision to perform a truly positive (wise) minimally invasive surgery               
 
o AND
 
 
 
- Achieving a cure for the patient, defined as normalization of serum calcium and PTH at one month and 6 months post-surgery
 
                                                                                                                                                                                                                                                                                                                                                                                                                                   |

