|                              | 
a discrepancy, the examinations will be reviewed in a Multidisciplinary Consultation Meeting (RCP), and the result of the review of the examination will be communicated to the surgeon.
 
Surgical decision for each diagnostic strategy
 
In case of positive results of the first and/or second exam, the surgery will consist of a minimally invasive procedure under extemporaneous, on an outpatient basis.
 
In case of negative imaging results (MIBI and FCH), an exploration of the 4 parathyroid sites will be performed.
 
In the case of multiple or ectopic PTAs, the surgical procedure will be adapted.
 
Histopathological examination of the surgical specimens will confirm the presence or absence of PTA.
 
The results of the imaging assessment will be compared with the surgical and pathological results.
 
Patients will be seen 1 and 6 months post-surgery with a blood test to assess normalization of serum calcium and PTH.
 |
| Sample size           | 
Considering that the proportion of patients referred to the right surgical strategy according to first-line imaging is 60% with MIBI SPECT/CT [Cheung, 2012] and 90% with FCH PET-CT [Quak, 2017], 50 evaluable patients (25 per arm) are needed to detect such a difference in proportions with a risk of 5% and a power of 80% (unilateral test). It is planned to include 58 patients to anticipate 15% of possible non-evaluable patients.
                                                                                                                                                                                                                                                                                                                                                                                                                                                                                                                                                               |

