## 6.2 SECONDARY ENDPOINTS

The secondary endpoints are:

- Average cost of caring for a patient for each of the two strategies
- Sensitivity, specificity, error rates, positive and negative likelihood ratios of FCH PET/CT and MIBI SPECT/CT
- Rate of minimally invasive surgeries and bilateral cervical explorations for each diagnostic strategy
- Number of failures of parathyroid surgery (regardless of the type of surgery performed), defined by the persistence of primary hyperparathyroidism 6 months after surgery
- Complications occurring within one month of surgery: infections, hematomas, laryngeal recurrent nerve injury
- Cohen's kappa coefficients between the 2 independent readers, during their first reading, then during their second reading (3 months later); as well as between the first and second reading of each of the 2 readers
- Serum PTH concentration at baseline
- To compare detection sensitivities of FCH PET-CT at 10 min and 60 min post-injection, as well as semi-quantitative analysis.
- Scores for the 6 dimensions (comfort, attention, information, pain management, waiting times, intimacy) of the EVAN-G questionnaire administered perioperatively (4 to 48 hours after the intervention before discharge from hospitalization)

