#### ❖ **Follow-up at 1 and 6 months after surgery**

**A laboratory assessment** including calcemia and PTH will be performed at 1 and 6 months after surgery.

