#### ❖ **Histopathological examination of surgical specimens**

Histopathological examination of the surgical specimens will confirm the presence or absence of PTA.

The results of the imaging assessment will be compared with the surgical and pathological results.

Patients will be seen again between 1 and 6 months post-surgery with a blood test to assess normalization of serum calcium.

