## 9 MEDICO-ECONOMIC STUDY

The medico-economic analysis will be carried out from the point of view of health insurance. From this perspective, only direct hospital costs will be included in the analysis. They will include the costs of diagnosis, the costs of surgery (type of surgical procedure, duration of intervention and hospitalization, anesthesia) and the cost of possible complications (hematomas, infections, damage to the recurrent laryngeal nerve, chronic hypoparathyroidism).

The efficacy endpoint will be the cure rate at one month (normalization of serum calcium at one month post-surgery). An incremental cost-effectiveness ratio will be estimated to establish the average cost needed to cure an additional person by moving from the usual strategy to the new strategy.

A sensitivity analysis of the uncertain parameters of the model will be performed to test the robustness of the cost-effectiveness ratio.

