## 11 STATISTICAL CONSIDERATIONS

### 11.1 SAMPLE SIZE

The primary endpoint is the proportion of patients for whom the first-line imaging technique (MIBI SPECT/CT or FCH PET/CT) allows guiding the surgical procedure appropriately, i.e. -say to decide on a true positive minimally invasive surgery and to obtain the patient's cure one month post-operatively.

Considering that the proportion of patients guided towards the right surgical strategy according to first-line imaging is 60% with MIBI SPECT/CT [Cheung, 2012] and 90% with FCH PET/CT [Quak, 2017], 50 evaluable patients (25 per arm) are necessary to detect such a difference in proportions with a risk of 5% and a power of 80% (one-sided test). It is planned to include 58 patients to anticipate 15% of possible non-evaluable patients. Based on the results of our published APACH-1 study [Quak, 2017] where a sensitivity of approximately 90% was observed with FCH PET/CT, we believe that a unilateral test is sufficient in the design of the design of APACH-2 to demonstrate the superiority of FCH PET/CT compared to MIBI SPECT/CT which has a sensitivity of approximately 60%.

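### The cure half of the primary endpoint has two definitions: normal calcium at 1 month (6.1), or normal calcium and PTH at both 1 and 6 months (synopsis)

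*Protocol*

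**What the plan says.** Section 6.1 of the protocol requires two things for a primary success: a true positive decision for minimally invasive surgery based on first-line imaging, and cure. It defines cure as follows: "Achieving a cure for the patient, defined as normalization of serum calcium at one month post-surgery".

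The synopsis (section 1, Main criterion) has the same two-part endpoint but defines the second part differently: "Achieving a cure for the patient, defined as normalization of serum calcium and PTH at one month and 6 months post-surgery".

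The other places that bear on cure are:

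- **Synopsis, paragraph on surgical decision and follow-up:** "Patients will be seen 1 and 6 months post-surgery with a blood test to assess normalization of serum calcium and PTH".
- **Section 9:** the efficacy measure for the economic analysis is calcium at one month, as in 6.1.
- **Section 11.1:** the sample size is built on "cure one month post-operatively", with no analyte named.
- **Section 11.2:** the primary comparison refers to cure with neither an analyte nor a time point.
- **Section 6.2:** surgical failure is a separate secondary endpoint, "defined by the persistence of primary hyperparathyroidism 6 months after surgery".
- **Section 7.4.3:** a laboratory assessment "including calcemia and PTH will be performed at 1 and 6 months after surgery".
- **Section 7.4.4, histopathology paragraph:** "Patients will be seen again between 1 and 6 months post-surgery with a blood test to assess normalization of serum calcium".

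**The concern.** The two definitions differ in analyte (calcium alone, or calcium plus PTH) and in timing (one month, or one month and six months). Each is written as the definition of the primary endpoint, and the protocol has no rule of precedence between synopsis and body.

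The trial is open-label and has a single primary test in 50 evaluable patients. Since 7.4.3 collects both analytes at both visits, both versions of the endpoint can be computed from the same data. Unless one is fixed in advance, the version reported as primary could be picked once the results by arm are known.

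The sample size is also tied to one pair of rates, 60% and 90%. The stricter rule can only give equal or lower rates in each arm, so the same pair cannot be assumed to hold for both versions.

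**Working it through.** **1. The definitions side by side**

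| Place in protocol | Analyte | Time |
|---|---|---|
| Synopsis, Main criterion | calcium and PTH | 1 month and 6 months |
| Synopsis, follow-up | calcium and PTH | 1 and 6 months |
| 6.1 Primary endpoint | calcium | 1 month |
| 9 Medico-economic study | calcium | 1 month |
| 11.1 Sample size | not named | 1 month |
| 11.2 Statistical analysis | not named | not given |
| 7.4.3 Follow-up (sampling schedule) | calcium and PTH | 1 and 6 months |
| 7.4.4 Histopathology | calcium | between 1 and 6 months |

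The synopsis rule adds conditions to the 6.1 rule. Every synopsis success is therefore a 6.1 success, but not the reverse. Three kinds of patient with normal calcium at one month change class: PTH raised at one month, calcium raised at six months, and PTH raised at six months.

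**2. The plan's own sample size**

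Inputs from 11.1: p1 = 0.60, p2 = 0.90, one-sided alpha 5% (z = 1.645), power 80% (z = 0.842). With the pooled-variance formula and p̄ = 0.75:

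n per arm = [1.645·√(2·0.75·0.25) + 0.842·√(0.60·0.40 + 0.90·0.10)]² / 0.30²

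= [1.007 + 0.483]² / 0.09 = 24.7, so 25 per arm and 50 in total.

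Power at 25 per arm is 80.4%. The stated figure reproduces, and it leaves almost no margin.

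**3. What the stricter rule could do**

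The documents do not say what share f of 6.1 successes would fail the synopsis rule. As an assumption, let f run from 5% to 30%, equal in both arms, so that the rates become 0.60(1 − f) and 0.90(1 − f). The number of patients who change class is 25·(0.60 + 0.90)·f = 37.5·f.

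| f | Rates | Power at 25 per arm | n per arm for 80% | Patients changing class |
|---|---|---|---|---|
| 0 | 60.0% v 90.0% | 80% | 25 | 0 |
| 5% | 57.0% v 85.5% | 73% | 31 | 1.9 |
| 10% | 54.0% v 81.0% | 66% | 37 | 3.8 |
| 20% | 48.0% v 72.0% | 54% | 51 | 7.5 |
| 30% | 42.0% v 63.0% | 44% | 69 | 11.3 |

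Exact enumeration of the uncorrected chi-square test gives 82%, 74%, 67%, 56% and 48% power for the same rows.

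**4. One trial, two readings**

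Suppose 15/25 v 22/25 succeed under 6.1. The pooled proportion is 37/50 = 0.74, so z = 0.28 / √(0.74·0.26·2/25) = 2.257 and one-sided p = 0.012.

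Remove about 20% of the successes: 15 becomes 12, and 22 loses 4.4, so it becomes 18 or 17.

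- 12/25 v 18/25: z = 1.732, p = 0.042.
- 12/25 v 17/25: z = 1.433, p = 0.076.

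One patient in one arm then decides on which side of 5% the result falls.

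**The case against.** The body of the protocol leans clearly one way. Wherever it gives cure a time point (6.1, 9, 11.1), that point is one month, and 11.1 restates the primary endpoint before sizing the trial on it. The rival definition appears only in the synopsis. The blood schedule in 7.4.3 does not prove that the primary endpoint uses month 6, because those samples are needed anyway for the six-month failure endpoint in 6.2. This is a good argument for which version to keep. It does not remove the other version from the synopsis, and 11.1 is silent on PTH. A statistical analysis plan that picked one would still contradict the other protocol text.

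The magnitude rests on an assumed range whose bounds the documents do not support. At f = 2% power would still be 77%. Section 11.1 also quotes about 60% and 90% as sensitivities, so it is not shown that these rates were derived for a composite with one-month calcium cure. Both points stand. The table shows the loss relative to the planning assumptions and does not forecast the trial's power. The worked example likewise does not show that the conclusion would reverse, because the nearer rounding (18/25) stays significant.

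Two further points should carry little weight. A one-month success who is a failure at six months under 6.2 is not in itself a fault, since the two endpoints measure different things. A patient lost after month 1 could be evaluable under one rule only, but the protocol does not define evaluable, and that handling may sit in the analysis plan.

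**Conclusion.** The concern holds. The trial's only confirmatory endpoint is defined twice in current text, with different analytes and time points, and nothing in the protocol settles which applies. The disagreement runs one way: the synopsis rule is the stricter of two nested rules.

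The contradiction needs no assumption. Its size does. If 5% to 30% of 6.1 successes failed the stricter rule equally in both arms, about 2 to 11 of the 37.5 expected successes would change class. Power would fall from 80% to between 73% and 44%, and 80% power would need 31 to 69 evaluable patients per arm instead of 25. This must be corrected before any comparison by arm.

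**What to change.** Amend the protocol so that one definition of cure appears in identical words in the synopsis, 6.1, 9, 11.1 and 11.2. It should name the analyte and the time point, and say how normal calcium with raised PTH is counted.

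**Preferred:** keep 6.1. Cure is serum calcium within normal limits at the one-month visit, whatever the PTH. Correct the synopsis to match, and name calcium plus PTH normal at both 1 and 6 months as a sensitivity analysis. This agrees with section 9 and with the timing in 11.1, and the sample size stays at 50 evaluable and 58 included.

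**Alternative:** keep the synopsis version and rewrite 6.1, 9, 11.1 and 11.2 to match. The assumed rates and the sample size must then be re-derived for that endpoint. If 10% of successes were reclassified, for example, the requirement would rise from 25 to 37 evaluable patients per arm.

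In the same amendment, correct the follow-up sentence in 7.4.4 so that it gives two visits, at 1 month and at 6 months, with both calcium and PTH measured, as in 7.4.3.

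The preferred route costs a wording amendment only. The samples it needs are already scheduled.
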